### 5.3 Strategies for Recruitment and Retention

Patients who attend any Allergy, Dermatology, Pediatrics, General Practitioner consults from the North region of Portugal and have the medical diagnosis of AD are invited to participate in the trial and contact the Immunology Department of Medical Faculty of Medicine. A screening visit is scheduled.

Advertisement trough media (television and newspapers ) invites patients from the general population with medical diagnosis of atopic dermatitis to contact the Immunology Department of Medical Faculty of Medicine and schedule a screening visit.

### 5.4 Treatment Assignment Procedures

##### 5.4.1 Randomization Procedures

##### Computer generated sequence

##### 5.4.2 Masking Procedures

Patients and investigator are provided with cotton t-shirts and pants coated and non coated with chitosan. Clothes are visual indistinguishable from each other and both patients and investigators are blinded to the intervention.

##### 5.4.3 Reasons for Withdrawal

A study subject will be discontinued from participation in the study if:

- Any clinical adverse event (AE), or other medical condition or situation occurs such that continued participation in the study would not be in the best interest of the subject.
- The subject meets any exclusion criteria (either newly developed or not previously recognized).
- Subjects are free to withdraw from participation in the study at any time upon request.

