### 3.2 Study Outcome Measures

##### 3.2.1 Primary Outcome

- Investigator rated eczema severity

Clinical improvement measured by local SCORAD (score of severity of AD- supplement 1) (initial versus final, % of change).

SCORAD is composed of three different domains (A= extension B= intensity C = subjective symptoms). To determine extent, the sites affected by eczema are shaded on a drawing of a body. The rule of 9 is used to calculate the affected area (A) as a percentage of the whole body: Head and neck 9% Upper limbs 9% each , Lower limbs 18% each , Anterior trunk 18% ,Back 18% 1% each for genitals, each palm and the back of each hand. The score for each area is added up. The total area is 'A', which has a possible maximum of 100%.

A representative area of eczema is selected. In this area, the intensity of each of the following signs is assessed as none (0), mild (1), moderate (2) or severe (3).:Redness ,Swelling ,Oozing / crusting Scratch marks , Skin thickening (lichenification),Dryness (this is assessed in an area where there is no inflammation) .The intensity scores are added together to give 'B' (maximum 18).

Subjective symptoms i.e., itch and sleeplessness, are each scored by the patient or relative using a visual analogue scale where 0 is no itch (or no sleeplessness) and 10 is the worst imaginable itch (or sleeplessness). These scores are added to give 'C' (maximum 20).

- Changes in Quality of life.

Patients are asked to answer the Portuguese version of the Dermatology Life Quality Index (> 16 years old) or the children´s Dermatology Quality of Life Index (4-16 years old) at the beginning and end of the study (supplement 2 and 3)

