## 4. Study Design

Double blind, placebo-controlled, parallel randomized study enrolling a sample of patients with medical diagnosis of AD.

The approximate time to complete study enrollment is about 6 months. The expected duration of subject participation is eight weeks, approximately, with one screening visit and two visits after enrollment, one at the beginning and the other at end of the study. During the eight weeks trial the patient will be asked to use cotton Tshirt and cotton pants as pijama during the night.

Visits are performed at an appropriate medical setting at Instituto Cuf, Porto. Each visit lasts approximately 45 min including medical examination, filling of one questionnaire, serum sampling and a superficial skin swab of determined areas.

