### 5.2 Subject Exclusion Criteria

A potential subject who meets any of the following criteria will be excluded from participation in this study if:

- Presence of any significant illness that could interfere with the study, particularly if accompanied by immunological skin abnormalities as psoriasis
- Contact eczema, hand eczema , nummular eczema, other forms of eczema that not atopic eczema
- Anything that, in the opinion of the investigator, preclude the subject’s full compliance with or completion of the study.

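### Section 5.4.3 ends study participation, not just garment use, for patients who newly meet an exclusion criterion, and provides no final SCORAD or quality-of-life assessment for them

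*Protocol*

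**What the plan says.** Protocol section 5.4.3 opens its list of withdrawal reasons with "A study subject will be discontinued from participation in the study if". The wording is mandatory, and it acts on the study rather than on wearing the textile. One listed reason is that "The subject meets any exclusion criteria (either newly developed or not previously recognized"). Another covers adverse events or other situations that make continuing contrary to the patient's interest. The third is the patient's own request.

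Section 5.2 supplies the exclusion criteria that the rule points to. One is "Contact eczema, hand eczema , nummular eczema, other forms of eczema that not atopic eczema". Another is open-ended: anything that the investigator believes would "preclude the subject’s full compliance with or completion of the study".

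Section 3.2.1 defines the SCORAD outcome as "initial versus final, % of change" and also lists change in quality of life, measured at the beginning and end, under the primary outcome. Section 4 sets about eight weeks of participation, "with one screening visit and two visits after enrollment, one at the beginning and the other at end of the study". Section 7 places the only SCORAD and quality-of-life assessments after baseline at Visit 2.

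**The concern.** The trial tests a coated textile worn against the skin every night. A contact reaction is a possible effect of that textile, and section 5.4.3 turns such a reaction into removal from the study. Poor compliance can also follow from how the garment feels or performs. These reasons arise after randomisation and may differ between arms because of the treatment itself.

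A patient removed before Visit 2 has a baseline SCORAD but, as the schedule stands, no final one. If those removed would have done worse than those who stayed, the patients left in the arm with more removals look better than the arm as randomised. Blinding does not prevent this. An investigator who applies the rule evenly, without knowing the arm, still removes more patients from the arm whose garment causes more reactions. A statistical analysis plan can say how missing values are handled, but it cannot recover an assessment that the protocol did not collect.

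**Working it through.** **Following one patient through the text**

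1. A randomised patient develops contact eczema in week 3. Section 5.2 lists contact eczema as an exclusion criterion.
2. Section 5.4.3 covers newly developed exclusion criteria and ends participation in the study.
3. Sections 4 and 7 describe no early-termination visit and no follow-up after discontinuation. No part of the protocol separates stopping the garment from leaving the study.
4. The section 3.2.1 outcome needs a final SCORAD, which is scheduled only at Visit 2. The patient would probably have none.

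**Inputs for the illustration**

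- From section 8.2: significance level 0.05, power 0.80, total 90. The section bases these on a difference of means and an SD but gives neither value, so the figure of 90 cannot be reproduced. It also does not state sidedness, the number per arm or a dropout allowance.
- Assumed: 45 per arm, two-sided test, removal rates as below, and removed patients 1 SD worse on the outcome than those retained in the same arm.

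**Detectable effect (normal approximation)**

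d = (z for alpha + z for power) × √(2/n per arm)

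- 45 per arm, two-sided: (1.960 + 0.842) × √(2/45) = 0.59 SD (0.60 with the t distribution)
- 45 per arm, one-sided: (1.645 + 0.842) × √(2/45) = 0.52 SD (0.53 with t)
- 90 per arm, two-sided: (1.960 + 0.842) × √(2/90) = 0.42 SD

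**Bias of a completer comparison**

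If a share p of an arm is removed and is 1 SD worse than the rest, the mean of the whole arm is worse than the completers' mean by p × 1 SD. The bias in the difference is therefore (p chitosan − p control) × 1 SD.

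**Power at the same losses**

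Power = Φ(0.591/SE − 1.960), with SE = √(1/n1 + 1/n2) in SD units. This shows the loss of precision alone, with the bias left out.

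| Removed, chitosan v control | Bias | Share of 0.59 SD | Completers | Overall loss | SE | Power |
|---|---|---|---|---|---|---|
| 10% v 2% | 0.10 − 0.02 = 0.08 SD | 14% | 40.5 + 44.1 = 84.6 | 6% | 0.218 | 77% |
| 20% v 5% | 0.20 − 0.05 = 0.15 SD | 25% | 36 + 42.75 = 78.75 | 12.5% | 0.226 | 74% |
| 10% v 10% | 0 | 0% | 40.5 + 40.5 = 81 | 10% | 0.222 | 76% |

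Against 0.42 SD, the first two shares become 0.08/0.42 = 19% and 0.15/0.42 = 36%.

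**False-positive rate when there is no true effect**

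Rate = Φ(bias/SE − 1.960) + Φ(−bias/SE − 1.960). For 10% v 2%, bias/SE = 0.08/0.218 = 0.37 and the rate is 0.066. For 20% v 5%, bias/SE = 0.15/0.226 = 0.66 and the rate is 0.10. The nominal rate is 0.05.

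**The case against.** The strongest reply is that few patients may be affected. Section 2.2.1 expects no adverse events from the coated textile and describes smooth cotton without dyes or sensitising preservatives. This stands as a reason not to assume a large bias. It is an expectation, though, and the protocol gives no rate. The illustrative rates are assumptions, and all the bias comes from the difference between arms: with equal removal and equally poor outcomes in those removed, it is zero.

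It may also be said that the protocol does not forbid a final SCORAD when a patient is discontinued. That is true, and it is why the loss is probable rather than certain. But nothing calls for one, and even an early value would not be a week-8 value.

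The protocol names no completer analysis, and the analysis set may properly be defined in a statistical analysis plan. That also stands. The point here is data collection, which such a plan cannot repair.

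Two stronger readings go too far. A reader might infer that the rule hides harm from the textile. Section 11.1 requires adverse events to be graded and assessed for causality, and section 11.2 enters adverse reaction data into the data system, so a reaction would still be recorded. A reader might also infer that the rule removes treatment failures as such. Worsening atopic dermatitis is not an exclusion criterion in section 5.2. It could lead to removal only through the compliance criterion or the adverse-event reason. Removal for poor compliance also biases the result only if the patients removed would have had different outcomes from those retained.

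**Conclusion.** The point holds in this form. As written, section 5.4.3 ends follow-up for reasons that can depend on the assigned garment, and those patients would probably lack the week-8 SCORAD and quality-of-life outcome. If removal is unequal and removed patients do worse, the error favours the arm with more reactions.

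Under the assumed rates and a 1 SD deficit, the bias is 0.08 to 0.15 SD. That is about 14% to 25% of a detectable effect of about 0.6 SD, which itself assumes 45 per arm and a two-sided test. Power at the matching losses is about 77% and 74%. None of these rates or effects comes from the protocol, and the bias could be negligible if reactions are rare or balanced.

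Severity: should-fix. The wording is clear and the remedy cheap, but the size is unknown and the adverse-event record is kept.

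**What to change.** Leave the clinical grounds in section 5.4.3 for stopping the garment unchanged. Add a paragraph stating that:

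- stopping the garment is not the same as leaving the study;
- every randomised patient who has not withdrawn consent attends Visit 2 at week 8 for SCORAD and quality of life, whether or not the garment is still worn and whether or not an exclusion condition has developed;
- these patients stay in their assigned arm for the primary comparison.

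Also reword the opening line of the section so that its clinical reasons end use of the garment, with only the patient's own withdrawal of consent ending participation.

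The cost is one paragraph and the effort of following patients who have stopped the garment. Visit 2 is already planned for every patient, so no new visit or measurement is needed. The change has to be made before enrolment, because week-8 assessments that were not done cannot be recovered later.

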##### 5.4.5 Termination of Study

The study ends when the sample size is achieved (approximately 90 patients)

This study may be prematurely terminated if, in the opinion of the investigators, there is sufficient reasonable cause.

Circumstances that may warrant termination include, but are not limited to:

- Determination of unexpected, significant, or unacceptable risk to subjects.
- Insufficient adherence to protocol requirements.
- Data are not sufficiently complete and/or evaluable.

## 6. Study Intervention/Investigational Product

### 6.1 Study Product Description

##### 6.1.1 Acquisition

Textiles will be provided by textile enterprise Crispim e Abreu Lda.

##### 6.1.2 Formulation, Packaging, and Labeling

Formulation, packaging, and labeling will be done as usual in textiles. No specific changes for the study protocol are required.

##### 6.1.3 Product distribution

Crispim e Abreu, Lda will assure storage and shipment of the material in adequate conditions to Immunology Department of Medical Faculty of Medicine.

### 6.2 Dosage, Preparation and Administration of Study Intervention/Investigational Product

Textile use will be performed according with the protocol .

### 6.3 Accountability Procedures for the Study Intervention/Investigational Product(s)

Textiles coated with chitosan will be distributed as frequent necessary for good progression of the study by Crispim e Abreu, Lda.

### 6.4 Concomitant Medications/Treatments

Patients are asked to maintain the

## 7. Study Schedule

Visit 0:

- Explain study protocol
- Review medical history to determine eligibility based on inclusion/exclusion criteria.
- Schedule visit 1

Visit 1 :

- Provide written information about the study
- Obtain signature of potential subject on written informed consent
- Perform medical examination and register SCORAD index
- Answer a quality of life questionnaire
- Patients are explained and given a diary symptoms card
- Perform skin swab of determined areas
- Perform serum sampling
- Patients are explained trial and are given a TShirt and pants
- Surveillance and medical care, if required

Visit 2 :

- Review medical history including medications history
- Perform medical examination and register SCORAD index
- Answer a quality of life questionnaire
- Deliver the diary symptoms card
- Perform skin swab of determined areas
- Perform serum sampling

## 8. Statistical Considerations

### 8.1 Study Hypotheses

The use of a textile coated with a natural biopolymer will improve clinical outcomes on patients with atopic dermatitis diminishing inflammatory biomarkers as well as the number of skin colonizing Staplylococcus aureus and expression of its virulence factors.

### 8.2 Sample Size Considerations

Considering a parallel trial with a significant level of 0.05 and statiscal power of 0.8 based on difference of means and standard deviation of outcome SCORAD the sample size calculated was 90 patients

## 9. Source Documents and Access to Source Data/Documents

The investigator will maintain appropriate medical and research records for this trial for the purposes of quality assurance reviews, audits, and evaluation of the study progress.

## 10. Ethics/Protection of Human Subjects

### 10.1 Ethical Standard

The investigator will ensure that this study is conducted in full conformity with the principles set forth in the Declaration of Helsinki.

### 10.2 Institutional Review Board

The protocol will be submitted for approval request by the Ethical Commission.

### 10. Informed Consent Process

Consent forms will be approved and the subject will be asked to read and review the document. Upon reviewing the document, the investigator will explain the research study to the subject and answer any questions that may arise. The subject will sign the informed consent document prior to any procedures being done specifically for the study. The subjects will have the opportunity to discuss the study with their surrogates or think about it prior to agreeing to participate. The subjects may withdraw consent at any time throughout the course of the trial. A copy of the informed consent document will be given to the subjects for their records. The rights and welfare of the subjects will be protected by emphasizing to them that the quality of their medical care will not be adversely affected if they decline to participate in this study. (Supplement 6)

##### 10.3.1 Informed Consent/Assent Process (in Case of a Minor)

Extensive discussion of risks and possible benefits of this procedure will be provided to the parents or subject’s legally authorized representative. Consent forms describing in detail the study procedures and risks are given to parents or subject’s legally authorized representative and written documentation of informed consent is required prior to starting intervention. Parents or subject’s legally authorized representative will be asked to read and review the document and sign prior to any procedure being done specifically for the study. (Supplement 7)

### 10.4. Exclusion of Special Populations

Children under twelve years-old .

### 10.5 Subject Confidentiality

Subject confidentiality is strictly held in trust by the participating investigators. This confidentiality is extended to the clinical information relating to participating subjects.

The study protocol, documentation, data, and all other information generated will be held in strict confidence. No information concerning the study or the data will be released to any unauthorized third party.

### 10.6 Study Discontinuation

In the event that the study is discontinued, patients will not be affected.

## 11. Data Handling and Record Keeping

The investigator is responsible to ensure the accuracy, completeness, legibility, and timeliness of the data reported. All source documents should be completed in a neat, legible manner to ensure accurate interpretation of data. Dark ink is required to ensure clarity of reproduced copies.

Copies of the electronic CRF (eCRF) will be provided for use as source documents and maintained for recording data for each subject enrolled in the study. Data reported in the eCRF derived from source documents should be consistent with the source documents or the discrepancies should be explained

### 11.1 Data Management Responsibilities

All source documents and laboratory reports must be reviewed by the clinical team and data entry staff, who will ensure that they are accurate and complete. Adverse events must be graded, assessed for severity and causality, and reviewed by the site investigator.

Data collection is the responsibility of the clinical trial staff. During the study, the investigator must maintain complete and accurate documentation for the study.

### 11.2 Data Capture Methods

Clinical data (including concomitant medications, and expected adverse reactions data) and clinical laboratory data will be entered into a data capture system. The data system includes password protection and internal quality checks, such as automatic range checks, to identify data that appear inconsistent, incomplete, or inaccurate. Clinical data will be entered directly from the source documents.

### 11.3 Types of Data

Data for this study will include age, gender, clinical data obtained by medical examination, and outcome measures – serum biomarkers, skin microbiological evaluation, quality of life data.

## 12. Publication Policy

Following completion of the study, the investigator is expected to publish the results of this research in a scientific journal.

###

## 13. Planning:

### 13.1 Chronogram

The Project has 2 years duration divided in four phases: planning, execution, analysis, conclusion

| **Phase** | **Date** | **Tasks** |
| --- | --- | --- |
| Planning/preparation | June –October 11 |  |
| Execution | November 2011-June 2012 | Patients inclusion |
| Analysis | July 2012-December 2012 | Data analysis |
| Conclusion | December 2012-June 2013 | Preparation and Manuscript submisson |

## 14. Funding

Funding supported by Serviço e Laboratório de Imunologia, Faculdade de Medicina da Universidade do Porto

